### 3.3 Calculation of the number of subjects

The number of subjects required to meet our main objective was calculated by assuming a bilateral test with an alpha risk of 5% and a beta risk of 20% (80% power). On the basis of REHPA survey data (Rolland Y et al. 2009), 13.5% of all residents reported in the REHPA survey were admitted to hospital services in 3 months, an estimate of 54% in 1 year. By limiting the population of the REHPA survey to subjects with the inclusion criteria defined in IDEM, 12% were admitted to hospital services in 3 months, an estimate of 48% at 1 year. According to the same survey, of the 48% of all hospitalizations, half were via ED. Indeed, we can estimate an incidence of ED transfers of 24% at 1 year in the non-intervention group. Assuming a 30% reduction in the ED transfer rate in the intervention group, the 12-month ED transfer rate will be 16.8%. 516 subjects are needed in groups, taking into account the cluster effect with an ICC set at 0.02 of an attrition rate of 20% (average known % of deaths per year from REHPA data), the minimum number of subjects per group varies from 950 to 1050 depending on the inflation factor linked to the contamination between the groups, which has been varied from 5 to 10%.

|                    |                                                                   |                                                                                                            |
|--------------------|-------------------------------------------------------------------|------------------------------------------------------------------------------------------------------------|
| Principal analysis | Statistical Analysis Plan (SAP)-IDEM Study 0910701
Version 1.0 | [figure not shown]
Hôpitaux de Toulouse |
|                    |                                                                   | 07/22/2016                                                                                                 |

In total, 1,000 residents per group or 2,000 residents must be included. Taking into account an inclusion number of 30 residents on average per NH, 35 institutions per arm are necessary. Given the potential of 240 NH of REHPA network, this number of institution is realistic to achieve. In total 89 nursing homes have volunteered.

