## 6 STATISTICAL ANALYZES

### 6.1 Principal analysis of the primary endpoint

The number and percentage of subjects who had at least one admission to a hospital ED in a one-year follow-up period will first be described by randomization group of the patient's NH (intervention or control) and in total.

The 1-year follow-up period for each subject begins at the end of the wave of inclusion in the center (i.e. start date of hospitalization collection).

The primary analysis of the effectiveness of management will compare the ED transfer rate between the two groups after a 1-year follow-up. To account for intra-center correlation (i.e., non-independence between observations of the same center) the effect of the intervention will be tested using a logistic regression model with random effects. The center randomization group (i.e. NH) subjects will be considered as a fixed effect and the center as a random effect

|                    |                                                                   |                                                                                                            |
|--------------------|-------------------------------------------------------------------|------------------------------------------------------------------------------------------------------------|
| Principal analysis | Statistical Analysis Plan (SAP)-IDEM Study 0910701
Version 1.0 | [figure not shown]
Hôpitaux de Toulouse |
|                    |                                                                   | 07/22/2016                                                                                                 |

to model the risk of a transfer to the ED. The risk of the first species for this main analysis is set at 5% (confirmatory test).

The intra-class correlation coefficient will also be calculated from this model.

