when they are hospitalized). Then, for each subject, the number of transfer to ED that occurred during the risk period will be counted. The incidence rate for each NH will be calculated as the total number of ED transfers divided by the sum of the at-risk follow-up times for the center's subjects and will be transformed per 100 person-years.

- Finally, a survival analysis will be carried out to study the delays until the occurrence of the event (i.e. first transfer to the ED). In this study, death is a competitive risk to consider in the analysis given that the risk of having an event after death is zero (i.e., no independence between the two risks). Standard Kaplan-Meier survival analyzes do not lead to valid results for a specific risk if failures for another cause are treated as censorship. A suitable method is the use of cumulative impact functions that represent the cumulative probability of failure due to a specific cause over time. Cumulative incidence functions will be calculated for each group considering the death as a competitive risk and the difference between the functions of the 2 groups and the 5% Alpha risk method will be tested (exploratory test). Cumulative incidence rates estimated at 1 year will be presented for each group with their 95% confidence interval. Deadlines will be calculated in days between the start date of follow-up and:
  - the date of first ED transfer for the subjects having had the event studied in the year or
  - the date of death for subjects who died in the year (subjects with competitive risk) or
  - the premature dropout date of the study if dropped out for a reason other than death before one year (censored subjects) or
  - the point date for the remaining subjects who will also be censored (i.e. end date of inclusions in the center plus 1 year)

Population of analysis: All complementary analyzes of the primary endpoint will be performed on the ITT population. The analysis of incidence rates will also be performed on the PP1 population.

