### 6.3.2 ED transfer during 18 months

The first admission to an ED within 18 months of the start of the follow-up will be the event considered.

The main analysis (logistic regression with random effects) and the additional analyzes planned on the main judgment criterion will be carried out again considering this time 18 months of follow-up for each subject.

To calculate incidence rates, the risk follow-up time for each subject will be the time in years between the start date of follow-up (i.e. end date of inclusions in the center) and the date of point (i.e. start date follow-up plus 18 months) or the premature dropout date of the study for subjects who stopped the study before 18 months of follow-up MINUS possible hospitalization times.

For the survival analysis, the time will be calculated in days between the start date of follow-up and:

- the date of first hospitalization in the emergency department for subjects having had the event studied within 18 months or
- the date of death for the subjects who died within 18 months without having gone to the ED beforehand (subject with competitive risk) or
- the premature dropout date of the study if dropped out for any reason other than death within 18 months (censored subjects) or

|                    |                                                                   |                                                                                                            |
|--------------------|-------------------------------------------------------------------|------------------------------------------------------------------------------------------------------------|
| Principal analysis | Statistical Analysis Plan (SAP)-IDEM Study 0910701
Version 1.0 | [figure not shown]
Hôpitaux de Toulouse |
|                    |                                                                   | 07/22/2016                                                                                                 |

- the date of the point for the remaining subjects who will also be censored (i.e. end date of the inclusions in the center plus 18 months)

Population of analysis: The main analysis will be carried out on the population ITT as well as on the populations PP1 and PP2. The additional analyzes will be done on the ITT, the analysis of the incidence rates will also be carried out on the PP1 and PP2 populations.

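### The competing-risk comparison of time to first ED transfer (SAP 6.2, repeated in 6.3.2) specifies no allowance for clustering by nursing home, in its test or in its confidence intervals

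*SAP*

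**What the plan says.** The SAP summary (Diagram of the Study) gives nursing homes (NHs) as the unit of randomisation, 1:1. Section 6.1 gives the principal logistic model a centre random effect and says why: "To account for intra-center correlation (i.e., non-independence between observations of the same center".

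The same care appears in the other between-group comparisons:

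- The adjusted model in 6.2 is a mixed logistic model.
- The incidence rates in 6.2 are computed home by home.
- The resident-level secondary endpoints in 6.3.3 to 6.3.7 and 6.3.9 use mixed models with centre as a random effect.
- The additional endpoints in 6.4 use a mixed logistic model.
- Staff burden (6.3.8) is compared at home level.
- The subgroup models in 6.7 extend the principal model.

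The last analysis in 6.2 is time to first ED transfer with death as a competing risk. It calls for one cumulative incidence function per group and an exploratory 5% test of the difference, and adds: "Cumulative incidence rates estimated at 1 year will be presented for each group with their 95% confidence interval". It names no test, variance estimator or interval method, and it does not mention centre. Section 6.3.2 extends this to 18 months: "the additional analyzes planned on the main judgment criterion will be carried out again considering this time 18 months of follow-up". That section redefines the times and censoring dates but adds nothing on clustering.

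**The concern.** The usual two-sample test for cumulative incidence functions, and the usual intervals for a cumulative incidence, take subjects as independent. Residents of one home share staff, physicians and transfer habits, and the SAP itself plans for a positive ICC. A programmer who follows 6.2 literally has no instruction to do anything but the ordinary analysis, because wherever the SAP wants centre handled it usually says so.

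At stake is how this analysis reads beside the primary one. Section 6.2 introduces it to deal with follow-up shortened by death and early withdrawal, so it will be read as a check on the primary result. Suppose the mixed logistic model is not significant and the competing-risk test falls just below 0.05. A reader could credit the better handling of follow-up when the cause is variation between homes that was left out of the standard error. The group intervals would also look more precise than the design allows.

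**Working it through.** **Inputs, all from SAP section 3.3**

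- Error rate and power: "assuming a bilateral test with an alpha risk of 5% and a beta risk of 20% (80% power".
- Control rate: "we can estimate an incidence of ED transfers of 24% at 1 year in the non-intervention group". A 30% relative reduction gives 16.8% in the intervention group.
- ICC 0.02 and 20% attrition: "taking into account the cluster effect with an ICC set at 0.02 of an attrition rate of 20".
- Cluster size: "Taking into account an inclusion number of 30 residents on average per NH, 35 institutions per arm are necessary".
- Alternative cluster size: 89 homes volunteered for a total of 2,000 residents, and 2,000 / 89 = 22.5 per home. This assumes that all 89 take part and the target is met.

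**Step 1. The plan's own figure.** The SAP states 516 per group before the cluster effect. For 24% against 16.8%, with z values 1.960 and 0.842:

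- Pooled proportion 0.204; difference 0.072.
- n = [1.960 × √(2 × 0.204 × 0.796) + 0.842 × √(0.24 × 0.76 + 0.168 × 0.832)]² / 0.072² = 491.
- With continuity correction: n/4 × [1 + √(1 + 4/(n × 0.072))]² = 518.

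The corrected value is within 2 of 516, so the inputs are read as the SAP meant them.

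**Step 2. Effect of leaving clustering out.**

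- Design effect: DE = 1 + (m − 1) × ICC, for m residents per home.
- True two-sided error of an unadjusted 5% test: 2 × [1 − Φ(1.96/√DE)].
- Coverage of an unadjusted 95% interval: 1 minus that error.

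For m = 30 and ICC 0.02, DE = 1 + 29 × 0.02 = 1.58 and √DE = 1.257. The error is 2 × [1 − Φ(1.559)] = 11.9% and the coverage 88.1%. For m = 22.5, DE = 1.429 and √DE = 1.196, so the error is 10.1% and the coverage 89.9%.

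| ICC | True error, 22.5 per home | True error, 30 per home |
|---|---|---|
| 0.005 (assumed) | 6.3% | 6.7% |
| 0.01 (assumed) | 7.5% | 8.4% |
| 0.02 (SAP) | 10.1% | 11.9% |
| 0.05 (assumed) | 17.4% | 21.1% |

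**Step 3. Check by simulation.** The formula is for a proportion, so a Gray-type test ignoring centre was run on 4,000 simulated null trials per scenario. Homes were beta-binomial with 24% ED transfer, 20% of the remaining residents died, and there was no other loss before one year.

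| Homes per arm × residents | ICC | Rejection rate | Coverage of the unadjusted 95% interval |
|---|---|---|---|
| 35 × 30 | 0 | 5.3% | 95.4% |
| 35 × 30 | 0.01 | 7.7% | 91.8% |
| 35 × 30 | 0.02 | 12.2% | 87.5% |
| 44 × 23 | 0.02 | 10.6% | 88.8% |

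A t-test on home-level proportions in the 35 × 30, ICC 0.02 scenario rejected 5.3% of the time. The excess error therefore comes from ignoring homes.

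**Step 4. What it does to a reported interval.** At 24% with 1,000 residents in a group, the unadjusted half-width is 1.96 × √(0.24 × 0.76/1000) = 2.6 points, giving 21.4% to 26.6%. Multiplied by 1.257 it is 3.3 points, giving 20.7% to 27.3%.

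**The case against.** The strongest reply is that the SAP is silent here rather than wrong. A reader might infer that it declares residents independent or prescribes an unclustered test. It does neither: no test is named, and the sentence describing it does not read cleanly, so a method may have been lost in translation. The incidence-rate test in 6.2 is also unnamed, yet it passes as cluster-aware because its rates are computed per home. This stands, and it limits the point to a missing specification. It does not remove the point. The unit described for the incidence rates is the home. For the cumulative incidence functions it is the group, and that leads to the ordinary analysis.

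A reader might also infer that the trial's conclusion is at risk, or that only this analysis deals with death. The documents do not support either. The one confirmatory test is the mixed logistic model, which has a centre effect. Under 6.1, a resident who dies without a transfer counts as a non-event and stays in the denominator. Without other losses, the 1-year cumulative incidence is that same proportion. The competing-risk analysis adds timing and the censoring of residents who leave for other reasons, and the home-level incidence rates also deal with shortened follow-up.

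The exploratory label limits the consequence further. But section 6.3.1 explains that label, for the secondary tests, by multiplicity. A label of that kind does not correct a standard error, and the intervals will be read as estimates in any case.

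Finally, it is tempting to shrink the cluster to 24 residents (30 × 0.8) for attrition. That is not justified: residents who leave after the first month stay in the ITT analysis, as events, deaths or censored times.

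**Conclusion.** The point holds as an omission of moderate severity. Sections 6.2 and 6.3.2 give the competing-risk test and its group intervals no allowance for clustering, unlike the SAP's other resident-level between-group models. If the ordinary methods are used, the true error of a 5% test is about 10% to 12% at the SAP's ICC of 0.02, and about 6% to 8% at 0.005 to 0.01. At 0.02 and 30 per home, intervals cover about 88% and should be 1.26 times wider.

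The direction needs only a positive ICC. The size rests on the planning ICC, on equal cluster sizes, and on 22.5 to 30 residents per home. The SAP gives no separate ICC for 18 months, so applying the same size there is an assumption. The ICC to be estimated under 6.1 will show where in the range the 1-year analysis falls. The confirmatory analysis and the sample size do not depend on this point.

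**What to change.** In 6.2 and again in 6.3.2, state that the competing-risk test and the confidence intervals of the cumulative incidences allow for clustering by nursing home, and name the method before the analysis begins. One suitable pair is a subdistribution-hazard model with variance clustered on home for the group effect, and a bootstrap that resamples whole homes within each group for the 12- and 18-month intervals. An equivalent cluster-aware method would serve as well.

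The cost is about two sentences in the SAP and a little programming, with no new data and no change to the primary analysis. The intervals will be wider, as the design requires.

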### 6.3 Analysis of the secondary endpoints

#### 6.3.1 General

All secondary endpoints will be previously described by NH randomization group of subjects (intervention or control) and in total. The quantitative criteria will be summarized by their

|                    |                                                                   |                                                                                                            |
|--------------------|-------------------------------------------------------------------|------------------------------------------------------------------------------------------------------------|
| Principal analysis | Statistical Analysis Plan (SAP)-IDEM Study 0910701
Version 1.0 | [figure not shown]
Hôpitaux de Toulouse |
|                    |                                                                   | 07/22/2016                                                                                                 |

mean, standard deviation, median, 1st and 3rd quartile (Q1 and Q3), minimum and maximum. For the qualitative criteria, the number and percentage corresponding to each category will be presented.

All statistical tests performed to meet the secondary objectives will be bilateral with a risk of the first species at 5%. All these tests will have to be considered as purely exploratory not guaranteeing a global risk on the study of 5% (multiplicity of the tests).

The 18-month follow-up period for the secondary endpoints begins at the end of the inclusion wave in the center (i.e., the start date for the collection of judgment criteria).

Population of analysis: The analyzes on the secondary criteria of judgment will be made on the subjects of the ITT population for which the endpoint is available, except if another population is defined explicitly.

### 6.3.2 ED transfer during 18 months

The first admission to an ED within 18 months of the start of the follow-up will be the event considered.

The main analysis (logistic regression with random effects) and the additional analyzes planned on the main judgment criterion will be carried out again considering this time 18 months of follow-up for each subject.

To calculate incidence rates, the risk follow-up time for each subject will be the time in years between the start date of follow-up (i.e. end date of inclusions in the center) and the date of point (i.e. start date follow-up plus 18 months) or the premature dropout date of the study for subjects who stopped the study before 18 months of follow-up MINUS possible hospitalization times.

For the survival analysis, the time will be calculated in days between the start date of follow-up and:

- the date of first hospitalization in the emergency department for subjects having had the event studied within 18 months or
- the date of death for the subjects who died within 18 months without having gone to the ED beforehand (subject with competitive risk) or
- the premature dropout date of the study if dropped out for any reason other than death within 18 months (censored subjects) or

|                    |                                                                   |                                                                                                            |
|--------------------|-------------------------------------------------------------------|------------------------------------------------------------------------------------------------------------|
| Principal analysis | Statistical Analysis Plan (SAP)-IDEM Study 0910701
Version 1.0 | [figure not shown]
Hôpitaux de Toulouse |
|                    |                                                                   | 07/22/2016                                                                                                 |

- the date of the point for the remaining subjects who will also be censored (i.e. end date of the inclusions in the center plus 18 months)

Population of analysis: The main analysis will be carried out on the population ITT as well as on the populations PP1 and PP2. The additional analyzes will be done on the ITT, the analysis of the incidence rates will also be carried out on the PP1 and PP2 populations.

### 6.3.3 The quantity and type of non-drug treatments

The modification of the prescription of a non-drug treatment will be modeled using a mixed logistic regression model with the randomization group as the fixed effect and the center as a random effect to estimate the impact of the group on the occurrence of the criterion.

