#### a- The quantity and type of non-drug treatments

The endpoint to meet this objective will be the changes of non-drug (paramedical) prescriptions such as physiotherapy, occupational therapy, psychomotricity, psychological counseling, dietetics, speech therapy or other care during the 18 months of follow-up since the inclusion (ie binary yes / no criterion). The changes will be analyzed first globally then separately for each type of care cited. The changes include stopping, increasing or decreasing the periodicity and the introduction of a care.

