## 6.2 Complementary analyzes of the primary endpoint

First, a second mixed logistic regression model will be used to study the effect of the intervention on the risk of admission to the ED in the first year, taking into account potential confounders of age, co-morbidities (Charlson), dependency (GIR score), antecedents of psychiatric pathologies and the presence of cognitive decline at inclusion. The effect of the intervention will be tested with a risk of 5% (exploratory test).

Then, in order to consider the differences in the duration of follow-up caused by the deaths and the anticipated stopping of study, other complementary analyzes will be conducted on the primary endpoint.

- Incidence rates defined as the number of emergency room admissions per 100 person-years (i.e. 100 persons followed exactly 1 year in NH) will be calculated for each NH and a statistical test will be performed to determine if the difference between the incidence rates in both groups is significant (exploratory test at 5%). To calculate incidence rates, the at-risk follow-up time for each subject will first be calculated as the time in years between the start date of follow-up (i.e. end date of inclusions in the center) and the date of point (i.e. start date of follow-up plus 1 year) or the date of premature dropout of the study for the subjects who stopped the study before 1 year of follow-up MINUS possible durations of hospitalization (i.e. the subjects are no longer at risk of transfer to the ED

|                    |                                                                   |                                                                                                            |
|--------------------|-------------------------------------------------------------------|------------------------------------------------------------------------------------------------------------|
| Principal analysis | Statistical Analysis Plan (SAP)-IDEM Study 0910701
Version 1.0 | [figure not shown]
Hôpitaux de Toulouse |
|                    |                                                                   | 07/22/2016                                                                                                 |

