### 6.3.6 The residents' process of entry into the dependency

The difference between the GIR scores at the end-of-study visit and during the inclusion visit will be compared between the 2 groups using a mixed model of covariance analysis (comparison of mean values by adjusting for the inclusion score). The randomization group and the inclusion score will be considered as fixed effects and the center as a random effect. The total score obtained on the 4 items of the Lawton IADL at the end-of-study visit will be compared between the 2 groups using a mixed model of analysis of variance (comparison of

|                    |                                                                   |                                                                                                            |
|--------------------|-------------------------------------------------------------------|------------------------------------------------------------------------------------------------------------|
| Principal analysis | Statistical Analysis Plan (SAP)-IDEM Study 0910701
Version 1.0 | [figure not shown]
Hôpitaux de Toulouse |
|                    |                                                                   | 07/22/2016                                                                                                 |

mean values). The randomization group will be considered as a fixed effect and the center as a random effect.

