### 6.5.3 Description of data collected at inclusion

The characteristics found in the randomized NH centers (randomization stratification factors, number of residents included) will first be described.

The following characteristics of the subjects identified for inclusion in the study will be described for the entire analysis population and will be described in the 2 groups (intervention, control):

- Criteria for inclusion and non-inclusion;
- Sociodemographic characteristics (age, sex, marital status, education, mother tongue (French yes / no), occupation (yes / no), seniority in the NH (in months);
- Medical history and associated pathologies (visual or auditory impairment, smoking and alcohol consumption, total Charlson Comorbidity Index score);

|                    |                                                                   |                                                                                                            |
|--------------------|-------------------------------------------------------------------|------------------------------------------------------------------------------------------------------------|
| Principal analysis | Statistical Analysis Plan (SAP)-IDEM Study 0910701
Version 1.0 | [figure not shown]
Hôpitaux de Toulouse |
|                    |                                                                   | 07/22/2016                                                                                                 |

- Cognitive antecedents (progressive decline yes / no, MMSE test yes / no and score, cognitive assessments yes / no and type of assessment);
- Family history of dementia (presence of family history of dementia yes / no);
- Hospitalizations during the last 3 months by type of hospitalization (planned or in emergency) and by type of service;
- Ongoing drug and non-drug treatments at inclusion by type of treatment;
- Anticipated prescriptions by type;
- GIR total score at inclusion.

The following results from the Comprehensive Geriatric Assessment (CGA) obtained during the inclusion visit only for the intervention group, will be described:

- Overall MMSE score;
- Results of the clock test (score and normality);
- Results of the Borson Mini-Cog (normality);
- Overall score of the 5 word test;
- Categorical verbal fluency test results (total words generated, total acceptable words);
- Confusion Assessment Method (CAM) test result (acute confusional state yes / no);

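### Section 6.3.3 omits receipt of the care at inclusion: the test stays valid, but power is given up and realised case-mix differences stay in the odds ratio

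*SAP*

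**What the plan says.** - **Outcome (SAP section 4.2, item a).** A yes/no indicator of any change in non-drug care over 18 months from inclusion. On what counts: "The changes include stopping, increasing or decreasing the periodicity and the introduction of a care". On the order of analysis: "The changes will be analyzed first globally then separately for each type of care cited".
- **Model (section 6.3.3).** The change "will be modeled using a mixed logistic regression model with the randomization group as the fixed effect and the center as a random effect". There is no other term.
- **Baseline data (section 6.5.3).** The items described at inclusion in both groups include "Ongoing drug and non-drug treatments at inclusion by type of treatment". Only the geriatric assessment results listed after them are restricted to the intervention group.
- **Adjustment elsewhere.** The GIR change in section 6.3.6 is analysed by a "comparison of mean values by adjusting for the inclusion score". For the primary endpoint, section 6.2 adds a covariate model: "a second mixed logistic regression model will be used to study the effect of the intervention on the risk of admission to the ED". Section 6.3.2 repeats it at 18 months. Neither step is extended to non-drug care.
- **Status (section 6.3.1).** All secondary tests are two-sided at 5% and declared exploratory.

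**The concern.** For one type of care, a resident who does not receive it at inclusion can only begin with an introduction. A resident who does receive it can only begin with a stop, an increase or a decrease. One change is enough for a yes, so the chance of a yes may depend heavily on baseline receipt. That status concerns care already in place at inclusion, and it is recorded in both arms.

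Leaving it out has two possible consequences. Differences between homes in baseline provision add to the between-home variance and can weaken the test. Any arm difference in baseline receipt that happens to occur passes into the estimated odds ratio. Both depend on receivers and non-receivers changing at different rates.

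The NPI, QOL-AD and IADL scores are listed at inclusion for the intervention arm only, so the same remedy is not evidently open to them. Here it is.

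**Working it through.** **Inputs from the SAP.** 35 homes per arm, 30 residents per home on average, 20% attrition and ICC 0.02 (section 3.3); outcome and model as above. The SAP states no change rate, baseline prevalence, between-home spread of provision or power for this endpoint. There is therefore no figure of its own to reproduce, and the rates below are assumptions.

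**Step 1: odds ratio under imbalance, no intervention effect.** Let q be the share receiving the care at inclusion, and b and a the change rates in receivers and non-receivers. The arm's change rate is p = q·b + (1 − q)·a. With q = 45% in one arm and 35% in the other:

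| b / a | p (q = 45%) | p (q = 35%) | Odds ratio |
|---|---|---|---|
| 30% / 20% | 0.135 + 0.110 = 0.245 | 0.105 + 0.130 = 0.235 | 1.06 |
| 35% / 15% | 0.1575 + 0.0825 = 0.240 | 0.1225 + 0.0975 = 0.220 | 1.12 |
| 50% / 10% | 0.225 + 0.055 = 0.280 | 0.175 + 0.065 = 0.240 | 1.23 |

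For the last row, (0.28/0.72) / (0.24/0.76) = 1.23. If b = a the odds ratio is 1 whatever the imbalance. A 5-point imbalance around 50% receipt gives 1.03 (30%/20%) to 1.10 (50%/10%).

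**Step 2: size of a chance imbalance.** In simulations with 35 homes per arm and 30 × 0.8 = 24 residents per home, the arm difference in receipt had an SD of about 0.053 when prevalence varied between homes (logit SD 1), and about 0.024 when it did not. A 10-point imbalance is then 0.10/0.053 = 1.9 SD in the first case and 0.10/0.024 = 4.2 SD in the second. With varying provision and rates of 50%/20% or 50%/10%, the unadjusted log odds ratio correlated 0.5 to 0.7 with the imbalance. The adjusted one correlated about 0.

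**Step 3: power.** A random-intercept logistic model was fitted with and without baseline receipt. The true odds ratio was 1.4, common to receivers and non-receivers, with 300 runs per row (error 2 to 3 points). For 24 residents per home, 50% receive the care and the home SD is √(0.02/0.98 × π²/3) = 0.26. For 30 per home, the home SD is 0.3.

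| Residents per home | Provision between homes (logit SD) | b / a | Power without | Power with |
|---|---|---|---|---|
| 24 | equal | 30% / 20% | 74% | 74% |
| 24 | equal | 50% / 20% | 73% | 76% |
| 24 | equal | 50% / 10% | 65% | 73% |
| 24 | 1 | 30% / 20% | 74% | 75% |
| 24 | 1 | 50% / 20% | 62% | 77% |
| 24 | 1 | 50% / 10% | 49% | 78% |
| 30 (40% receive) | 1.2 | 35% / 15% | 61% | 72% |
| 30 (40% receive) | 1.2 | 50% / 10% | 42% | 72% |

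A tenfold contrast (20% receive, 50% against 5%) gave 25% to 64%. That is an extreme case and should not carry the argument.

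**Step 4: effect through introductions only.** With 24 per home, 40% receiving, rates 35%/15%, and an odds ratio of 1.8 in non-receivers and 1.0 in receivers (200 runs), power moved from 70% to 70% (provision SD 0.5) and from 56% to 60% (SD 1.2). With 1.8 and 0.8 at SD 1.2 it moved from 26% to 28%.

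**Step 5: type I error.** With 30 per home (200 runs), the null rejection rate was 3–6% unadjusted and 4–7.5% adjusted. With 24 per home (300 runs, error about 1.3 points), it was 4.0–9.0% and 3.3–8.3%, averaging 6.2% and 5.6% over eight scenarios. Any excess over 5% is similar in both models, so it is not produced by omitting baseline receipt.

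**The case against.** Much of the opposing case stands.

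- **Validity.** A reader might infer that the planned test is invalid or its odds ratio biased. The SAP does not support that. Homes are randomised, so chance imbalance averages out and the confidence interval allows for it.
- **Selective inclusion.** The home's own physician conducts the inclusion visit, and intervention residents also have the geriatric assessment. Arms could therefore differ through who is included. But the SAP says all eligible residents are included and describes preselection in both groups. Nothing shows that an imbalance arose, and the 45% against 35% is assumed. Section 6.5.3 would make one visible.
- **Precision.** It is tempting to say that adjustment always narrows the interval. It does not. With equal provision and rates of 50%/20%, the standard error rose from 0.113 to 0.121 while power rose slightly. With varying provision it fell, from 0.133 to 0.122. Power is the better measure.
- **One odds ratio.** A baseline main effect still pools introductions with stops, increases and decreases under one arm effect. It removes baseline differences but does not separate the events.
- **Global analysis.** There, any resident can gain some type of care, so the argument about which change is possible is looser. The count covariate was not simulated.
- **Convention.** Sections 6.3.4 and 6.3.9 also use arm and centre only, and adjusting a change score such as GIR is more routine than adjusting a binary outcome.

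None of this removes the point that a baseline variable recorded in both arms, and tied directly to the outcome's definition, is left out of the model.

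**Conclusion.** The point holds as a matter of efficiency and of how the estimate reads. Section 6.3.3 uses arm and centre only, and no other section adds baseline receipt to this model. In the simulations, power with the baseline term was about equal or higher throughout. The gain was nil to about 30 points, or more in the most extreme case. It was near nil when change rates were close, modest when provision was even across homes, and small when the effect came only through introductions. With no effect, a 10-point imbalance gives an odds ratio of about 1.06 to 1.23, and exactly 1 if both groups change equally often. All of these sizes rest on assumed rates. The reasoning is exact for the by-type analyses and weaker for the global one. The endpoint is secondary and exploratory, so the change is worth making but the planned test is not wrong.

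**What to change.** In section 6.3.3, add baseline status as a fixed effect:

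- in each by-type model, receipt of that care at inclusion (yes/no);
- in the global model, the number of ongoing non-drug care types at inclusion, with its functional form stated.

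Keep the arm-and-centre model as a secondary display, and name it as the fallback where a type is too rare for the adjusted model to converge. Section 7 excludes imputation, so also say how residents without a baseline care record enter the model, for example through a not-recorded category. Write this before the analysis starts: section 2 says the analysis will not be blind, and a covariate chosen afterwards would look driven by the results.

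The cost is a sentence or two in the SAP and a variable already collected. The odds ratio becomes conditional on baseline care, and sparse types may not support the extra term. Some adjusted fits failed to converge in one simulated scenario (rates 50%/10%, varying provision, no effect).
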